## Abstract

**Background:**

Human immunodeficiency virus (HIV) remains a major public health challenge in sub‐Saharan Africa, including Ethiopia. Adults living with HIV are at increased risk of liver‐related complications, poor treatment outcomes, and suboptimal virological control, particularly when adherence to antiretroviral therapy (ART) is inadequate. Patient‐centered education has emerged as a promising strategy for improving treatment adherence, self‐management, and health outcomes among individuals with chronic diseases. However, evidence on the effect of patient‐centered education on HIV virological outcomes among adults living with HIV remains limited, particularly in resource‐constrained settings such as North‐West Ethiopia. Furthermore, limited evidence exists regarding the feasibility and acceptability of structured educational interventions tailored to this vulnerable population. This pilot quasi‐experimental study therefore aims to assess the effect of a patient‐centered education intervention on HIV virological outcomes among adults living with HIV in North‐West Ethiopia.

**Objective:**

To evaluate the feasibility and preliminary effectiveness of a patient‐centered educational intervention on HIV virological outcomes, medication adherence, and HIV‐related knowledge among 120 adult people living with HIV–HBV co‐infection receiving ART in North‐West Ethiopia.

**Methods and Analysis:**

This pilot quasi‐experimental study will employ non‐randomized intervention and comparison groups with baseline and 6‐month follow‐up assessments. A total of 120 participants (60 per group) will be enrolled from selected hospitals in North‐West Ethiopia. Participants in the intervention group will receive a structured patient‐centered education program integrated into routine ART services, while the comparison group will continue receiving standard care. Quantitative data will be entered into EpiData version 4.6 and analyzed using STATA version 18. Descriptive statistics will summarize baseline characteristics. Baseline differences between groups will be assessed using chi‐square tests for categorical variables and independent t‐tests or non‐parametric equivalents for continuous variables. The primary outcome will be the change in log‐transformed HIV viral load (log_10_ copies/mL) from baseline to the end of the 6‐month follow‐up period. The intervention effect will be evaluated using paired t‐tests, difference‐in‐differences analysis, and multivariable linear regression while adjusting for potential confounders, including age, sex, educational status, baseline viral load, duration of ART, and medication adherence. Virological suppression, defined as HIV viral load < 1000 copies/mL, will be assessed as a secondary clinical outcome. Secondary outcomes will include medication adherence, HIV‐HBV‐related knowledge, self‐management practices, and retention in care. Statistical significance will be declared at *p* < 0.05. A qualitative study will be conducted at the end of the intervention period to assess the feasibility, acceptability, and implementation potential of the intervention. Qualitative data will be collected through focus group discussions with adult people live with HIV, in‐depth interviews with healthcare providers, and key informant interviews with hospital leaders and program managers. Audio‐recorded interviews will be transcribed verbatim and analyzed using directed thematic analysis with MAXQDA version 20.

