#### Secondary Objectives

2.1.2

To assess the effect of the patient‐centered education intervention on medication adherence to ART and HBV‐active medications among adults living with HIV‐HBV co‐infection.

The corresponding secondary outcome will be medication adherence, measured using the context‐adapted Hill‐Bone Medication Adherence Scale (HBMAS) and analyzed using both continuous adherence scores and categorical adherence levels (good vs. poor adherence).

To evaluate changes in participants' knowledge and awareness regarding HIV following the patient‐centered education intervention.

The corresponding secondary outcome will be the HIV‐HBV‐related knowledge score, measured using a structured questionnaire and reported as a composite score, with higher scores indicating better knowledge and awareness.

To assess the effect of the patient‐centered education intervention on retention in HIV care among adults living with HIV‐HBV co‐infection.

The corresponding secondary outcome will be retention in care, measured by participants' attendance at scheduled clinic visits, continuity of follow‐up care, and adherence to routine clinical monitoring throughout the 6‐month study period.

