#### Patient‐Centered Health Education Intervention

2.9.1

The intervention selected for this study is a patient‐centered health education intervention designed to improve HIV‐related clinical outcomes among adults living with HIV receiving ART. The intervention package consists of structured patient‐centered health education, medication adherence counseling, behavioral counseling, and self‐management support integrated into routine ART services. The primary goals of the intervention are to improve HIV virological outcomes, enhance medication adherence, strengthen self‐management practices, increase disease‐related knowledge, promote healthy behavioral changes, and improve retention in care.

Following participant enrollment, six healthcare professionals from the selected hospitals, including nurses, pharmacists, and clinicians involved in HIV care, will undergo a 3‐day training program. The training will focus on patient‐centered communication, HIV management, medication adherence counseling, behavioral change strategies, and delivery of standardized health education materials to ensure consistent intervention implementation.

Participants in the intervention group will receive structured education sessions over a 6‐month period during routine ART clinic visits. The initial session will last approximately 40–60 min and will cover general information about HIV‐HBV co‐infection, treatment goals, medication adherence, viral load monitoring, risk reduction strategies, and self‐management practices. Subsequent follow‐up sessions will be conducted monthly, with each session lasting approximately 20–30 min, to reinforce key messages, address barriers to adherence, provide individualized counseling, and support behavioral change.

Educational sessions will be delivered using standardized counseling guides, visual educational materials, and interactive discussions tailored to participants' needs, literacy levels, and clinical circumstances. Family members or treatment supporters may be involved in selected sessions, where appropriate, to strengthen adherence support. A detailed description of the intervention components, delivery procedures, and educational content will be provided following completion of the pilot study.

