#### Medication Adherence Counseling

2.9.3

Participants will receive structured education and counseling from trained healthcare professionals on the importance of taking medications as prescribed, the potential consequences of poor medication adherence, and the clinical benefits of maintaining optimal adherence to ART and HBV‐active medications. The counseling will emphasize how consistent medication use contributes to improved virological outcomes, reduced risk of disease progression, prevention of drug resistance, and better overall health outcomes.

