##### Patient Demographics and Treatment Variables

2.12.2.1

A structured data abstraction form and interviewer‐administered questionnaire will be used to collect participants' socio‐demographic, clinical, behavioral, and treatment‐related information under the supervision of the research team, which includes the principal investigator, a statistician, a clinical pharmacist, and senior medical experts. Trained research nurses will collect the data, while the principal investigator will oversee data quality through regular monitoring and validation.

Variables to be collected include age, sex, duration since HIV diagnosis, duration on ART, baseline and follow‐up HIV viral load, CD4 count, HBV serological status, comorbidities, concurrent medications, medication adherence, Health Belief Model (HBM) constructs, retention in care, and HIV–HBV‐related knowledge scores. These variables will be recorded at baseline and reassessed at the 6‐month follow‐up to evaluate changes over time and estimate the effect of the intervention.

Data will be obtained from participant interviews, patient medical records, laboratory reports, pharmacy refill records, and health facility electronic databases where available. All collected data will be anonymized by assigning unique study identification numbers before analysis to ensure participant confidentiality. Electronic datasets will be securely stored on password‐protected computers accessible only to authorized members of the research team.

Ethical approval will be obtained from the Institutional Review Board of the University of Gondar. Written informed consent will be obtained from all participants before enrollment. Permission to use standardized questionnaires and assessment tools will be secured from the respective developers or authorized sources prior to data collection.

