To estimate the adjusted intervention effect while accounting for repeated measurements within individuals and potential confounding, mixed‐effects linear regression models with random intercepts for participants will be fitted for each outcome. Fixed effects included group (intervention vs. comparison), time (baseline vs. endline), and the group‐by‐time interaction, with the interaction term representing the DiD estimate of the intervention effect. Models will adjust for clinically relevant covariates, including age, sex, religion, marital status, educational level, residence, WHO clinical stage, opportunistic infections, treatment interruption, alcohol use, smoking status, and condom use. Adjusted beta (β) coefficients with their corresponding 95% confidence intervals (CIs) were reported.

Model assumptions, including normality of residuals, linearity, homoscedasticity, independence of observations, and multicollinearity, were evaluated before model interpretation. Random‐effects assumptions will be assessed using the estimated variance components and intraclass correlation coefficient (ICC). All statistical tests were two‐sided, and statistical significance will be declared at *p* < 0.05.

Because this is a pilot quasi‐experimental study with a relatively small sample size, greater emphasis will placed on the magnitude and precision of the estimated intervention effects, expressed as adjusted β coefficients and 95% confidence intervals, rather than statistical significance alone. These findings are intended to inform the design and sample size estimation of future adequately powered randomized or multicenter intervention studies.

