This study has several methodological limitations. The intervention and control groups are recruited from only two health facilities, with one facility serving as the intervention site and the other as the control site. As a result, differences in outcomes may reflect not only the effect of the intervention but also underlying site‐specific characteristics, making it challenging to fully separate intervention effects from facility‐level influences. In addition, the inclusion of only two sites precludes the use of clustering‐adjusted analytical approaches such as mixed‐effects models or generalized estimating equations. Although multivariable analyzes will be performed to adjust for measured baseline differences between groups, residual confounding arising from unmeasured participant‐ or facility‐level factors may remain. Therefore, the study findings should be interpreted cautiously, taking into account the potential impact of unmeasured site‐specific influences.

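### Medication adherence, an outcome and the intended mechanism, is listed as a confounder with no baseline restriction, and section 2.15 gives a conflicting adjusted model

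*Protocol article*

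**What the plan says.** The abstract (Methods and Analysis) evaluates the intervention effect with paired t-tests, difference-in-differences (DiD) and multivariable linear regression "adjusting for potential confounders, including age, sex, educational status, baseline viral load, duration of ART, and medication adherence". Viral load is the only item in that list marked as a baseline value.

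Elsewhere the protocol gives adherence two other roles. Section 2.1.2 makes it an endpoint: "The corresponding secondary outcome will be medication adherence". Section 2.9.1 sets the package's goals as to "improve HIV virological outcomes, enhance medication adherence, strengthen self‐management practices", and section 2.9.3 has counsellors explain that "consistent medication use contributes to improved virological outcomes". Section 2.12.2.1 includes adherence in a list of which it says: "These variables will be recorded at baseline and reassessed at the 6‐month follow‐up".

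Section 2.15 describes a different adjusted analysis. It is a mixed linear model with a random intercept per participant and terms for group, time and their interaction, "with the interaction term representing the DiD estimate of the intervention effect". Its twelve covariates are age, sex, religion, marital status, education, residence, "WHO clinical stage, opportunistic infections, treatment interruption, alcohol use, smoking status, and condom use". None carries a time point. Adherence and ART duration are absent, and baseline viral load enters only as the time-zero outcome.

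One sentence in the Discussion (section 3) bears on timing: "multivariable analyzes will be performed to adjust for measured baseline differences between groups".

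**The concern.** A confounder precedes the intervention. A variable that the intervention is designed to change, and through which it is expected to act, is a mediator once measured at follow-up. Adjusting for it then estimates only the part of the effect that bypasses it, and opens a path for bias from unmeasured causes of both adherence and viral load. The dataset will hold both the baseline and the 6-month adherence score, and the abstract does not say which one enters the regression.

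The two descriptions also differ in model type and in covariates. Section 2.15 places most emphasis on the adjusted coefficients and their confidence intervals, and intends them to inform the design and size of later trials. Two unreconciled specifications leave room to choose after the data are seen, and an attenuated coefficient would mislead that planning.

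**Working it through.** **The two specifications side by side**

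| | Abstract | Section 2.15 |
|---|---|---|
| Model | Multivariable linear regression | Random-intercept mixed model; effect = group-by-time term |
| Shared covariates | Age, sex, education | Age, sex, education |
| Only here | Baseline viral load, ART duration, medication adherence | Religion, marital status, residence, WHO stage, opportunistic infections, treatment interruption, alcohol, smoking, condom use |
| Marked as baseline | Viral load only | None |

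Three covariates are shared, three appear only in the abstract and nine only in section 2.15.

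**Effect scale.** Section 2.7 assumes an SD of change of 15 and a difference of 8.4. Its own figure reproduces: n = 2 × 15² × (1.96 + 0.84)² / 8.4² = 3528 / 70.56 = 50 per group. The standardised effect is 8.4 / 15 = 0.56 SD. Section 2.7 does not tie these values to log10 copies/mL, so 0.56 serves only as a convenient scale here.

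**Case 1: follow-up values are entered.** Let T be the total effect and m the share that passes through adherence. Conditioning on the change in adherence, or on baseline plus follow-up adherence, leaves T × (1 − m). The protocol gives no m, so the full range is shown. The simulated columns come from change-score regression with 400,000 simulated participants per row, the groups being balanced on baseline adherence.

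| m (assumed) | 0.56 × (1 − m) | No adherence term | Baseline adherence only | Baseline + follow-up | Follow-up only |
|---|---|---|---|---|---|
| 0 | 0.56 | 0.557 | 0.557 | 0.557 | 0.556 |
| 0.25 | 0.42 | 0.560 | 0.561 | 0.422 | 0.491 |
| 0.50 | 0.28 | 0.562 | 0.562 | 0.282 | 0.422 |
| 0.75 | 0.14 | 0.555 | 0.557 | 0.138 | 0.344 |
| 1.00 | 0.00 | 0.564 | 0.564 | 0.001 | 0.282 |

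Entries are sizes of the reduction in SD units. Follow-up adherence alone removes less, because it does not fully capture the change in adherence, but it still attenuates.

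The random-intercept model behaves in the same way. In one simulated data set of 1,200 participants with m = 0.50, the interaction was 0.638 with no adherence term, 0.638 with baseline adherence and 0.340 with time-varying adherence.

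**Case 2: baseline values are entered.** The table shows no loss of effect. For the section 2.15 model, however, consider a participant with both visits and a covariate X fixed at baseline. Subtracting the two rows gives

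Y(post) − Y(pre) = time effect + DiD × group + (X − X) × coefficient.

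The last term is zero. With complete pairs the interaction is estimated from these differences alone, so a baseline main effect cannot move it. The simulation agrees: with and without baseline adherence, the interaction was identical to four decimals in all five runs (for example 0.5722 and 0.5722 at m = 0.25). Participants with only one visit can shift it slightly, which is why the adjustment is almost nil and not exactly nil. A baseline imbalance between the two hospitals that predicts change in viral load would therefore remain essentially unadjusted.

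**The case against.** The case for a benign reading has substance. The Discussion speaks of baseline differences, and section 2.12.5 refers to baseline covariates, although for the adherence outcome. A missing baseline label proves little, since age and sex carry none either. Section 2.15, the fuller account, does not include adherence at all. Section 2.12.2.1 does not name treatment interruption, opportunistic infections, alcohol or condom use among the reassessed variables; only the general statement in section 2.12.2 about clinical and behavioural information covers them. That education acts through treatment interruption is inferred from the adherence and retention goals. An unadjusted DiD is also planned and is unaffected. All of this stands, and it limits the point.

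A reader might infer that the adjusted analysis conditions on both adherence and treatment interruption and would wipe out the effect. The documents do not support that. No single model contains both variables, the timing is left open, and only the mediated share would be lost, with total loss requiring full mediation. Nor is either model labelled primary, so it goes too far to say that the plan has two primary models. Losses of power computed from assumed mediation shares would be illustrations only: the shares are not in the protocol, and the residual SD would itself change on conditioning.

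The objection does not remove the conflict between the two lists or the unrestricted adherence term in the abstract. The baseline reading that it relies on also makes the section 2.15 adjustment nearly inert.

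**Conclusion.** The point holds in a limited form. The abstract calls a variable a confounder that the protocol treats as outcome and mechanism, without restricting it to baseline, and section 2.15 specifies a different model and list. The consequence depends on timing that neither place fixes. With follow-up or time-varying values, the adjusted estimate can lose up to the mediated share: from 0.56 SD to 0.42, 0.28 or 0.14 SD for assumed shares of 25, 50 or 75%. With baseline values nothing is lost, but the section 2.15 model then adjusts the DiD for almost nothing when pairs are complete. Neither reading delivers what the plan wants, which is a total effect adjusted for baseline differences between two hospitals. The size rests on assumed mediation shares and on section 2.7's 0.56 SD as a scale; the conflict and the missing time point rest on the text alone.

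**What to change.** State one adjusted model and one covariate list, identical in the abstract and section 2.15, and say that every covariate is the value recorded before the first education session. Enter adherence and treatment interruption as pre-intervention values or leave them out.

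Use a form in which baseline covariates can affect the DiD: either regress the change in log10 viral load on group and baseline covariates, or add covariate-by-time terms to the mixed model. When merging the lists, say how baseline viral load is handled. In the mixed model it is already the time-zero outcome. As a covariate in a change-score regression it turns the analysis into ANCOVA, which in a non-randomised comparison generally estimates something different from the stated DiD.

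Keep follow-up adherence for the exploratory analysis of relationships in section 2.10.3.

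The cost is wording in two places and slightly more model terms. Adherence is already measured at baseline (section 2.12.1), and the sample size does not change.

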**International Trial Registration Number:**

The intervention protocol was registered on 15 November 2025 with the Pan African Clinical Trials Registry under identification number PACTR202512648125852.

AbbreviationsAASLDAmerican Association for the Study of Liver DiseaseADEsadverse drug eventsAIDSacquired immune deficiency syndromeALTalanine aminotransferaseAORadjusted odds ratioARTantiretroviral therapyCHIVchronic hepatitis BCIconfidence intervalsCONSORTconsolidated standards of reporting trialsDAAsdirect‐acting antiviralsDNAdeoxyribose nucleic acidEFAexploratory factor analysisETVentecavirFGDfocus group discussionGFIgoodness‐of‐fit indexHAARThighly active antiretroviral therapy and HBeAb Hepatitis B(e) antibodyHBeAghepatitis B e‐antigenHBsAghepatitis B surface antigenHCChepatocellular carcinomaHCPshealth care providersHIVhuman immunodeficiency virusHRQoLhealth‐related quality of lifeIDIin‐depth interviewIFN‐ainterferon‐alphaIQRinterquartile rangeIRBInstitutional Review BoardIVintra veinousJBIJoana Brig's InstituteKIIskey informantLMICslow‐and middle‐income countriesMAXQDAMAX qualitative data analysisMCSmental component summaryMeSHmedical subject headingsMHmental healthMOPsmanual of operating proceduresNAsnucleotide analogsNUCsnucleotide analogs,OPDout patient departmentPCPsprimary care providersPCSphysical component summaryPFphysical functioningPLHIVpeople living with HIVSDstandard deviationsSFsocial functioningSSASub‐Saharan AfricaSVRsustain virological responseTDFtenofovir disoproxil fumarateWHOWorld Health Organization.

## Introduction

1

Human immunodeficiency virus (HIV) infection remains one of the major global public health concerns, particularly in sub‐Saharan Africa where the burden of disease is disproportionately high [1]. Hepatitis B Virus (HBV) infection is also highly endemic in the region, and co‐infection with HIV is common because both viruses share similar routes of transmission, including sexual contact, blood exposure, and mother‐to‐child transmission [2]. HIV has become an important clinical and public health issue because it accelerates disease progression, complicates treatment outcomes, and increases morbidity and mortality among affected individuals [3].

Globally, approximately 38 million people are living with HIV, and nearly 7%–10% of them are co‐infected with chronic HBV infection [2]. In Ethiopia, studies have reported varying prevalence rates of HIV ranging from 5% to 20% among people receiving antiretroviral therapy (ART) services [4, 5]. The presence of HBV among people living with HIV contributes to rapid liver disease progression, hepatocellular carcinoma, poor immune recovery, and increased risk of treatment failure [6, 7].

The primary goal of ART is achieving sustained HIV virological suppression, which improves quality of life, decreases HIV transmission, and reduces mortality [8]. However, maintaining viral suppression among HIV‐HBV co‐infected patients remains challenging because of poor medication adherence, inadequate counseling, psychosocial barriers, low health literacy, and co‐morbid conditions [9]. Studies from Ethiopia and other African countries indicate that suboptimal adherence remains one of the strongest predictors of virological failure among ART users [10, 11].

Patient‐centered education is increasingly recognized as an effective strategy to improve adherence and treatment outcomes among patients with chronic illnesses. Patient‐centered educational interventions involve individualized counseling, shared decision‐making, behavioral support, and tailored health information that addresses patients' specific needs and challenges [12]. Evidence suggests that educational interventions can improve ART adherence, retention in care, self‐management practices, and viral suppression among people living with HIV [13, 14]. Despite these benefits, limited evidence exists regarding the effectiveness of patient‐centered education specifically among HIV‐HBV co‐infected adults in resource‐limited settings such as Ethiopia.

North‐West Ethiopia is among the regions with a substantial burden of HIV infection and expanding ART services. However, there is inadequate evidence regarding intervention‐based approaches aimed at improving virological suppression among HIV‐HBV co‐infected individuals in the region. Therefore, this pilot quasi‐experimental study seeks to evaluate the effect of patient‐centered education on HIV virological suppression among adult people living with HIV in North‐West Ethiopia. The study findings may provide preliminary evidence for designing larger intervention studies and integrating patient‐centered educational strategies into routine HIV care programs.

Several studies have documented that HIV negatively affects treatment outcomes and overall health status among people living with HIV. HIV infection accelerates HBV replication and liver disease progression, while HBV co‐infection contributes to increased hepatotoxicity and impaired immune recovery during ART [6, 7]. Research has also shown that co‐infected individuals are more likely to experience poor HIV virological suppression compared with HIV mono‐infected patients [15].

In Ethiopia, evidence indicates that hepatitis co‐infection is associated with lower rates of viral suppression and higher levels of treatment complications among ART users [11]. Poor adherence to ART medications has consistently been identified as a major contributor to virological failure [10]. Studies conducted in sub‐Saharan Africa revealed that patients who receive regular counseling and educational support demonstrate significantly better adherence and viral suppression outcomes than those receiving routine care alone [13, 14].

Patient‐centered education has been widely recommended as a key strategy for chronic disease management because it improves patients' knowledge, motivation, communication, and participation in care [12]. In HIV care settings, individualized counseling and adherence‐focused interventions have shown positive effects on treatment retention and medication adherence [9]. Furthermore, integrated care approaches for HIV and HBV management have demonstrated feasibility and acceptability in low‐resource settings [16].

The World Health Organization and Ethiopian national HIV treatment guidelines emphasize the importance of adherence counseling, continuous patient education, and psychosocial support as essential components of comprehensive HIV care [2, 17]. Nevertheless, implementation of structured patient‐centered educational interventions specifically targeting HIV‐HBV co‐infected individuals remains limited in many healthcare settings.

Although evidence exists regarding the epidemiology and clinical outcomes of HIV‐HBV co‐infection, major gaps remain concerning effective behavioral and educational interventions for improving virological suppression among co‐infected patients. Most previous studies conducted in Ethiopia focused on prevalence, associated factors, and clinical characteristics of HIV rather than intervention‐based strategies [4, 5].

There is limited evidence on whether patient‐centered education can significantly improve HIV virological suppression among adults living with HIV in resource‐constrained settings. Existing studies on adherence interventions mainly target general HIV populations without specifically addressing the unique challenges faced by HIV‐HBV co‐infected individuals, such as liver‐related complications, treatment burden, stigma, and complex medication management [15].

Additionally, little is known about the feasibility and acceptability of implementing structured patient‐centered educational interventions within routine ART clinics in North‐West Ethiopia. Health facilities in the region often experience shortages of trained healthcare providers, limited counseling resources, and high patient loads, which may affect the delivery and sustainability of such interventions [17].

Furthermore, evidence is scarce regarding the extent to which culturally tailored educational interventions can influence patients' adherence behavior, knowledge, self‐management practices, and long‐term virological outcomes among HIV‐HBV co‐infected populations in Ethiopia. Therefore, this pilot quasi‐experimental study is intended to address these knowledge gaps and generate preliminary evidence to inform future large‐scale intervention studies and healthcare policy development.

